#### Missing data

In our experience, missing data is unavoidable. However, every effort will be made to minimize and appropriately handle missing data. Follow-up data will be gathered regardless of whether the intervention was received, and follow-up will be vigorously pursued to minimize missing data. Participants will be followed independent of whether they are engaged in PrEP care. If a participant is re-incarcerated during the follow-up period, we plan to work with the correctional facility to continue to follow them and avoid loss to follow-up. In addition, we will request permission to collect data from medical records for participants who do not complete a follow-up.

Whenever possible, we will collect and summarize the reasons participants drop out of the study. We will also evaluate missing data to determine if there are mechanisms that help to explain why data are missing and will utilize multiple imputation techniques [61]. Variables collected at baseline, such as demographic information, alcohol and drug use prior to incarceration, and HIV risk behaviors prior to incarceration, will be compared between participants retained throughout the study and participants who missed follow-up appointments. To increase confidence in our findings, sensitivity analyses will be performed with and without the missing data, using imputed data from the individuals with whom we lose contact.

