#### Phase 3: pilot RCT

For the pilot RCT, 80 participants will be recruited and assigned to a condition using a 3:1 ratio, with 60 participants assigned to MI-NAV and 20 participants assigned to SOC. Participants in the SOC condition will also meet with a study interventionist twice while incarcerated. During the first session, SOC participants will receive a pamphlet regarding PrEP during incarceration and will be informed that they can initiate PrEP by speaking with a provider from the correctional facility. Mirroring MI-NAV, the second session will occur 2 weeks before the participant is released from incarceration. This session will involve a referral to community-based PrEP care if the participant is interested and referral to community-based SUD treatment when appropriate. Participants will be randomly assigned to condition using urn randomization; the urn blocking variable will be baseline level of HIV risk behavior as assessed by the HIV Risk Assessment Battery (RAB) [42]. The 3:1 randomization ratio will allow us to maximize the information gained about the MI-NAV intervention while including a comparison condition. RCT participants will complete a baseline interview while incarcerated and follow-up interviews at 1, 3, and 6 months post-release from incarceration. Baseline and follow-up interviews will be conducted by research assistants who will be blind to participants’ assigned condition. RCT participants will receive gift cards in the amount of $25, $30, and $50, respectively, for the 1-, 3-, and 6-month follow-ups (see Table 1 for timing of Phase 3 protocol elements). No compensation will be provided for the baseline interview or sessions/check-ins with the interventionist.

**Table 1 Tab1:** Timing of participant enrollment, receipt of intervention, and assessment activities during Phase 3

Timepoint	Enrollment	Baseline	Post-allocation		
	− t1	0	+ 1 month	+ 3 months	+ 6 months
Enrollment					
Eligibility screen	X				
Informed consent	X				
Allocation		X			
Interventions					
MI-NAV					
SOC		X			
Assessments					
Primary outcomes			X	X	X
Secondary outcomes			X	X	X
Other outcomes		X	X	X	X

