##### PrEP care initiation and linkage to care

Information will be extracted from participants’ medical records at the correctional facility regarding whether PrEP was prescribed and whether PrEP was administered each day during the period of incarceration. Linkage to community-based PrEP care is operationalized as receipt of a prescription for PrEP from a community-based provider within 3 months of release from incarceration, verified through medical record data extraction. This time window was selected because it is consistent with the CDC’s guidelines for PrEP follow-up visits (every 3 months) [38].

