Data analysis will follow a sequence designed to examine the primary outcome questions: (1) Does MI-NAV lead to higher rates of linkage to community-based PrEP care? (2) Does MI-NAV lead to better PrEP adherence, based on dried blood spot tests (DBS), compared to SOC? (3) Does MI-NAV lead to better retention in care compared to SOC? There is little expectation of observed HIV seroconversion, given the modest sample size and 6-month follow-up window. However, seroconversion rates of each condition will be examined. Analyses will also be conducted to examine the relative impact of MI-NAV versus SOC on self-reported PrEP adherence. Following the intention-to-treat principle, all randomized participants will be included in the analyses. We anticipate an attrition rate less than 10%, which will provide us with a final sample size of at least 54 participants in the MI-NAV condition and 18 participants in the SOC condition. This estimate is based on previous research with a high-risk, incarcerated population, in a geographically similar setting, which retained 96% of participants at 12-month follow-up [54]. In addition, we will employ retention strategies that increase retention rates in this population [55], including: (1) offering interview incentives that are higher than normal hourly rates of pay and providing transportation to and from interview locations; (2) conducting regular phone check-ins or sending letters between appointments to ensure contact information has not changed; (3) collecting contact information of secondary contacts, such as friends or relatives, that will know how to reach the participant; and 4) working with local criminal justice agencies, parole officers, and police departments that can help maintain or reestablish contact with participants if necessary.

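### The one named missing-data sensitivity analysis, with versus without imputation, does not test loss that depends on the unobserved outcome, so agreement is not evidence of robustness to informative dropout

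*Protocol article*

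**What the plan says.** The Missing data section of the protocol article plans multiple imputation, a look at mechanisms that might explain the gaps, and a summary of dropout reasons where these can be had. Baseline variables "will be compared between participants retained throughout the study and participants who missed follow-up appointments". To strengthen trust in the results, "sensitivity analyses will be performed with and without the missing data, using imputed data from the individuals with whom we lose contact". No other missing-data sensitivity analysis is named, and the assumption behind the imputation is not stated.

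The Primary RCT analyses section fits generalized estimating equations (GEE) to whatever time points are available. The Phase 3 section randomises 80 women, "with 60 participants assigned to MI-NAV and 20 participants assigned to SOC". Planned data analysis expects attrition below 10% and hence a "final sample size of at least 54 participants in the MI-NAV condition and 18 participants in the SOC condition", citing earlier research "which retained 96% of participants at 12-month follow-up".

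Outcome sources differ. Linkage is "verified through medical record data extraction", and retention in care also comes from medical records. For women who miss follow-up, "we will request permission to collect data from medical records for participants who do not complete a follow-up". Dried-blood-spot samples are taken at 3 and 6 months from women prescribed PrEP, and self-reported adherence is asked at follow-up interviews. Both need contact with the woman.

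**The concern.** The two versions being compared are an analysis of available data and an analysis with imputed values. Standard imputation draws a lost woman's outcome from retained women with similar observed data (missing at random, MAR). If a woman is lost because of something not recorded that also determines whether she is in PrEP care (missing not at random, MNAR), neither version sees it. Agreement between them then says nothing about that risk.

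The risk is not remote here. The article itself links substance use and depression to poor treatment engagement, and lists barriers to care after release. Intervention contact also differs by arm: MI-NAV women are offered an accompanied first community appointment and monthly check-ins for 6 months, while SOC women are described as having two sessions in custody. The tie between staying in contact and being in care could therefore differ by arm, and this is what distorts a comparison. The pilot's declared goal is an effect-size estimate for planning a larger trial, so a bias that the check cannot show would be carried forward.

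**Working it through.** **Inputs from the article.** 60 MI-NAV and 20 SOC; attrition taken at the 10% ceiling. No linkage rates are given, so those below are assumptions.

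**The article's own figure.** 60 × 0.90 = 54 and 20 × 0.90 = 18. Both reproduce, leaving 6 + 2 = 8 women lost.

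**Do the two versions agree while the truth varies?** Assume 27/54 and 6/18 linked among retained women.
- Without imputation: (27/27) / (6/12) = 2.00.
- With within-arm MAR imputation the expected rates stay at 50% and 33.3%, so the odds ratio is again 2.00.

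If linkage were unknown for all 8 lost women:

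| Lost women | MI-NAV | SOC | Risk difference | Odds ratio |
|---|---|---|---|---|
| None linked | 27/60 | 6/20 | 15 points | 1.91 |
| All linked | 33/60 | 8/20 | 15 points | 1.83 |
| Only SOC linked | 27/60 | 8/20 | 5 points | 1.23 |
| Only MI-NAV linked | 33/60 | 6/20 | 25 points | 2.85 |

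For other assumed rates the range is 1.09 to 3.28 around 2.11 (16/54 vs 3/18), 1.41 to 3.36 around 2.38 (38/54 vs 9/18), and 0.67 to 1.49 around 1.00 (27/54 vs 9/18).

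**Can both versions agree on a wrong answer?** Let p be true linkage, and m1 and m0 the loss probabilities of linked and unlinked women. Linkage among retained women is p(1−m1) / [p(1−m1) + (1−p)(1−m0)]. Within-arm MAR imputation reproduces this rate. Take p = 0.40 in both arms (true odds ratio 1.0) and 10% loss per arm.
- MI-NAV loses only unlinked women (m0 = 0.10/0.60): 0.40/0.90 = 44.4%. SOC loss is random: 40%. Odds ratio 0.80/0.667 = 1.2.
- MI-NAV as above, and SOC loses only linked women (m1 = 0.10/0.40): 0.30/0.90 = 33.3%. Odds ratio 0.80/0.50 = 1.6.
- Only unlinked women lost in both arms: odds ratio 1.0, but both rates read 44% where the truth is 40%.

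**Size against sampling error.** For 27/54 vs 6/18 the standard error of the log odds ratio is √(1/27 + 1/27 + 1/6 + 1/12) = 0.569, giving a 95% interval of 0.66 to 6.10. The range 1.23 to 2.85 lies inside it.

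**Effect of obtaining records.** With u1 and u0 women unascertained in MI-NAV and SOC, the range of the risk difference has width u1/60 + u0/20. At 6 and 2 this is 10 + 10 = 20 points, matching 5 to 25 in the table. If records settled half of them (3 and 1, assumed), it would be 5 + 5 = 10 points. One SOC woman counts for 5 points and one MI-NAV woman for 1.7.

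**Adherence.** If a share f of an arm's values is missing and the missing values truly lie d below their imputed values, the arm mean is overstated by f × d. With f = 0.10 and d = 1 SD (both assumed) in one arm only, the difference moves by 0.1 SD. Records cannot narrow this.

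**The case against.** The strongest reply is that this is detail for an analysis plan. The article does not say that the imputation assumes MAR, and a fuller document, not shown, may specify the model and departures from it. That stands to this extent: silence on the model is not the finding. The point is narrower. The article does fix one check and give it a purpose, and as worded that check does not reach MNAR loss.

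The second reply is that primary linkage is record-based, that records of non-completers will be sought, and that under 10% loss is a modest threat beside the sampling error of 54 versus 18. This stands too. The 8-woman calculation is therefore an upper limit for linkage at the stated attrition. The commonest worry, that lost women are simply not in care, moves the example only from 2.00 to 1.91 (16.7 to 15 points). The wide ends need opposite outcomes in the two arms.

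Several stronger readings are tempting and not supported:
- **The check can reveal no informative loss at all.** Unweighted GEE needs stricter assumptions than MAR imputation, so a gap between the versions could expose loss related to observed variables. Only dependence on the unobserved outcome stays hidden.
- **At most 8 women enter the baseline comparison, so its power can be computed as 8 versus 72.** The article contrasts women retained throughout with those who missed appointments. A woman who misses one of three visits and returns would fall in the second group, so its size is not fixed by the attrition rate.
- **The article says that agreement between these two versions raises confidence.** It gives confidence as the aim of the analysis. Its explicit remark about similar results concerns intention-to-treat versus as-treated.

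**Conclusion.** The point holds in limited form. Under standard imputation, the planned with/without comparison can agree on 2.00 while the lost women's outcomes allow 1.23 to 2.85, or agree on about 1.2 to 1.6 when the true odds ratio is 1.0. Agreement should not be read as robustness to informative dropout. This rests on assumed linkage rates, on loss at the 10% ceiling, and on no departure from MAR being built into the imputation. Exposure is greatest for dried-blood-spot and self-reported adherence. For linkage and retention it is confined to women whose records cannot be obtained. In this pilot the effect is moderate and lies within the sampling interval, although that interval makes no allowance for such a bias. The change is a cheap improvement, not a correction on which the trial depends.

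**What to change.** Keep the planned comparison, which is a legitimate check on loss related to observed variables, and add two analyses.

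1. For linkage and retention, count women whose records cannot be obtained as not linked and not retained. Beside it, give a by-arm table of best and worst cases in whole-number counts, built on the number actually unascertained and not on the number who missed interviews.
2. For adherence among women prescribed PrEP, use multiple imputation with a downward shift varied separately by arm. Scoring every missing woman as having no detectable drug would not fit, because samples are taken only from women prescribed PrEP.

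Add one sentence saying that agreement with and without imputation is not evidence against loss that depends on the unobserved outcome.

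The cost is one extra table, some wording and a wider reported range. No new data are needed.

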## Discussion

Women with criminal-justice involvement are among the most vulnerable and heavily impacted by HIV [1], consistently reporting high rates of both sex and drug risk behavior [2, 3, 62, 63]. The link between risk behavior and incarceration is unsurprising given that many of the behaviors that place women at risk for HIV, such as injection drug use and transactional sex, also put them at risk for incarceration. Further, the time immediately following release from incarceration appears to be a particularly high risk period for HIV-related risk behavior among women [4–6]. PrEP can be a highly effective means of preventing HIV infection among at-risk women [9–11]. Currently, PrEP is underutilized among US women who are at risk for HIV [12, 14]. This protocol seeks to address the great need to engage women at risk for HIV in PrEP care, capitalizing on a period of incarceration as an opportunity to reach a high-need, vulnerable population.

While this study will advance our knowledge of barriers and facilitators to PrEP care among women at risk for HIV upon release from incarceration, there are some limitations that warrant recognition. First, since the goals of the study are to establish effect size estimates and to determine the feasibility and acceptability of the intervention, a modest sample size will be recruited. Therefore, it is unlikely that we will find statistically significant differences between treatment conditions. Second, due to the pilot nature of the current study, recruitment will occur at a single correctional facility. This impacts our ability to generalize the findings to other correctional settings and locations. If the intervention appears to be effective at promoting uptake of PrEP during incarceration and linkage to PrEP care post-incarceration, future research should employ a significantly larger sample size and multi-site recruitment to address these limitations.

Despite the aforementioned limitations, this study has the potential to significantly inform the field. Since risk of acquiring HIV is disproportionate within this population relative to others due to both elevated rates of sex and drug risk behavior, it is essential to develop tailored interventions that reduce their HIV risk as they reenter the community. Therefore, engaging at-risk women in PrEP care before and after release from incarceration has the potential to reduce their risk of acquiring HIV. However, women recently released from incarceration experience many barriers to receiving care, including substance use, stigma, and lack of transportation [28, 29, 64]. To be effective, an intervention will need to consider these barriers in order to facilitate linkage with community-based treatment. If successful, the MI-NAV intervention will increase uptake and linkage to PrEP care and thereby substantially reduce HIV seroconversion among this population. More broadly, if this treatment approach is effective, it could be applied to other types of treatment post-incarceration, such as treatment for SUD.

## Abbreviations

PrEP: pre-exposure prophylaxis
MI-NAV: motivational interviewing and patient navigator intervention
SOC: standard of care
